#### Recruitment, data collection, and compensation (US samples)

Participants are recruited through a combination of participant databases housed at the University of California, Riverside, and Boston University; targeted Facebook ads; community outreach; and personal outreach to religious leaders and organizations in the local areas surrounding the two campuses.

Given the ongoing COVID-19 pandemic and the high levels of access and exposure to computer technology, data collection in the US is being conducted entirely online. The Child Protocol is administered via live video chat between a researcher and the participating child. The session is recorded via Zoom (except in cases where the parent/caregiver or child declines to be recorded), and the researcher also logs most of the child’s responses in real-time via Qualtrics survey software. In some cases, the Caregiver-Child Conversation task is completed independently and asynchronously by parents/caregivers and children without live supervision by a researcher, and parents/caregivers submit an audio recording of this conversation to the research team via email. In other cases, the researcher administers the task to parents/caregivers and children at the end of the Child Protocol, or in a separate live video chat. Finally, parents/caregivers complete an online version of the Parent Survey independently and asynchronously via Qualtrics.

To thank participants, families are given one $20 e-gift card for each participating child upon completion of the Child Protocol, and an additional $20 gift card when the parent/caregiver completes the Caregiver-Child Conversation task and the Parent Survey. For families with more than one child participating, parents/caregivers receive an additional $10 gift card for completing the Caregiver-Child Conversation and Parent Survey with each additional child.

(Please note that recruitment, data collection procedures, and compensation vary substantially across the rest of the cultural-religious samples represented in the network, and will be provided in forthcoming manuscripts.)

### Overview

#### Protocol components

The study consists of three components: (1) the Child Protocol, (2) the Caregiver-Child Conversation task, and (3) the Parent Survey; see Fig 2 for overview. For the full text of all materials (as adapted for the five target religions included in US samples), all visual stimuli, and Qualtrics survey (.qsf) files, please visit the following OSF repository: https://osf.io/dumf4/.

**Fig 2 pone.0292755.g002:**
[figure not shown]
Overview of the full Developing Belief Network Wave 1 study protocol for children (ages 4–10 years) and their parents or other primary caregivers. Depicted here is the default order of study protocol components. First, the participating child completes the Child Protocol. Parts 1 and 2 of the Child Protocol are administered in the same testing session for some children (including most US children 8 years old or older), and in two testing sessions on different days for other children (including all US children under the age of 8 years). The order of the two Memory Span tasks (digit span and word span) is determined randomly for each child. Within each task, blocks labeled with numbers (i.e., “Block 1, Block 2,…”) are presented in the fixed order shown here, and blocks labeled with letters (i.e., “Block A, Block B,…”) are presented in a random order for each child. Second, the child and their parent/caregiver participate in a Caregiver-Child Conversation task. In some cases, this task is completed on the same day as the Child Protocol, and in other cases it is completed on a different day. Third, the child’s parent/caregiver completes the Parent Survey. Different samples of parents/caregivers are shown different subsets of the tasks marked as “optional”; US caregivers complete all of the tasks shown here. Any parents/caregivers who have more than one child participating in the study complete an abbreviated Parent Survey for the second (third, etc.) child, consisting of only the survey elements marked with one asterisk (*) as well as shortened or otherwise modified versions of the survey elements marked with two asterisks (**). “Indiv. Diff.” = Individual Difference.

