In the Middle East, the study is being administered in Arabic (with limited code-switching to French and English as needed) to Maronite Catholics, Orthodox Christians, Protestant Christians, Shia Muslims, and Sunni Muslims living throughout Lebanon, as well as members of the Druze faith living in and around the Chouf Mountains, Lebanon (PI: [name]; co-PI: [name]); in Hebrew to Modern Orthodox Jewish people living in and around Tel Aviv, Israel (PI: [name]; co-PIs: [name] and [name]); and in Arabic to Muslim Arab people living in Central and Northern Israel (PI: [name]; co-PIs: [name] and [name]).

In sub-Saharan Africa, the study is being administered in Rutooro to Anglicans and Catholics living in and around Kabarole, Uganda (PI: [name]); and in Xitsonga and Sepedi to Christians with a range of syncretic traditional Southern African beliefs and practices living in the rural villages surrounding Tzaneen, South Africa (PI: [name]; co-PIs: [name] and [name]).

In South Asia, the study is being administered in Hindi to Hindus and Muslims living in Vadodara, Gujarat, India (PI: [name]; co-PIs: [name] and [name]).

In Southeast Asia, the study is being administered in English to Buddhists and Muslims living in Singapore (PI: [name]; co-PIs: [name] and [name]); and in Indonesian to Muslims and Christians (Protestants and Catholics) living in Jakarta, Indonesia, and to Hindus and Muslims living in Bali, Indonesia (PI: [name]; co-PI: [name]).

Finally, in East Asia, the study is being administered in Mandarin Chinese (written in Simplified Chinese) to religiously unaffiliated people living in and around Shanghai, China (PI: [name]; co-PIs: [name] and [name]); and in Mandarin Chinese (written in Traditional Chinese) to people who engage in a range of Buddhist, Taoist, and Yiguandao beliefs and practices living in and around Hsinchu, Taiwan R.O.C. (PI: [name]; co-PI: [name]).

The DBN is planning for three waves of data collection, following the same samples of children over the course of three years. This manuscript focuses on the methods for Wave 1, which will shed light on development via cross-sectional comparisons of ages. Future waves of data collection will complement this cross-sectional approach with longitudinal analyses of individual children.

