#### Eligibility, inclusion, and exclusion criteria (US samples)

US samples are being recruited through the University of California, Riverside, and Boston University, using a shared set of eligibility, inclusion, and exclusion criteria.

To be eligible for inclusion, a family must currently live within driving distance of one of the two university campuses. Although data collection for Wave 1 in the US is remote due to the ongoing COVID-19 pandemic (see “Recruitment, data collection, and compensation [US samples],” below), this geographical restriction is intended to allow for in-person participation for future waves of data collection. Participating children must be between the ages of 4 years 0 months and 10 years 11.99 months at the time of the initial study session. Children must speak English or Spanish, and parents/caregivers must read and respond in writing in English or Spanish. Participating parents/caregivers must be parents or legal guardians of the participating child; multiple siblings from the same family are allowed to participate. Finally, parents/caregivers must report that children are either (a) being raised in one of the following religious traditions: Protestant Christianity, Catholicism, the Church of Jesus Christ of Latter-day Saints, Islam, or Judaism; or (b) being raised in no religious tradition (i.e., the child is religiously unaffiliated). Children who are being raised in other religious traditions (e.g., Buddhism, Hinduism, Orthodox Christianity, or Sikhism) are ineligible for the study; in these cases, families are thanked for their interest, and invited to participate in other studies in the relevant lab.

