** *Non-reference group (Religion Block)* **					
*plural noun form*	Muslims	Muslims	Muslims	Christians	Christians
*adjective form*	Muslim	Muslim	Muslim	Christian	Christian

Unaffiliated children in the US are shown the version of the protocol that corresponds to the religion with which they are likely most familiar (see main text for details). See main text for descriptions of network-wide guidelines for item selection. “L.D.S.” stands for “Latter-day Saints.”

*Parallel tasks with parents/caregivers*. Parents/caregivers complete the religion block of the Social Essentialism task (but no other blocks of this task), and they are asked to indicate their level of certainty for each response on an 11-point scale ranging from [0] “I am not sure at all” to [10] “I am extremely sure.”

*Planned analyses*. Based on previous work [64, 68, 69], we hypothesize that we will observe the highest levels of social essentialism in the gender block and the lowest levels of social essentialism in the wealth block, and that social essentialism in the religion block will be intermediate between these extremes. To test this hypothesis, we will examine the main effect of domain (gender, religion, wealth) on children’s tendency to select “essentialist” responses.

Developmentally, we hypothesize that these differences in social essentialism across domains will increase with age [see, e.g., 68]. To test this hypothesis, we will examine statistical interactions between domain (gender, religion, wealth) and participant age (4–10 years).

In testing these predictions, we plan both to conduct item-level analyses (e.g., examining differences across the four questions included within each domain, or examining domain differences considering each of these four questions separately); and to conduct analyses in which we combine responses across items.

Beyond these predictions, we plan to compare the responses of boy and girl participants, especially in the gender block; to compare responses of children from families varying in socioeconomic status, especially in the wealth block; to compare responses across samples from different cultural-religious groups in all blocks; to compare children’s responses to those of parents/caregivers; to explore relationships between children’s responses in this task and information provided in the Parent Survey; and to examine relationships between this and other tasks included in the Child Protocol.

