#### Direct questions about religion

Building on previous work on the development of religious and ethnic identity [e.g., 61, 79–82], we include a set of questions designed to directly assess children’s explicit understanding of religion and their own religious identity. This is the final task in the Child Protocol; see Fig 2.

*Task design and procedure*. The task begins with the researcher saying, “The last thing I want to do is ask you a few questions about religion. I might use some words that you don’t know, and if that happens that’s totally okay, just let me know and we’ll skip that one. I might also ask you some questions that seem really silly or obvious to you, or I might even ask you the same thing a few different times—that’s because I’m talking to really little kids too and I need to ask it a few different ways.” The child is then presented with a set of questions in a fixed order, proceeding roughly from most open-ended and general to most close-ended and specific.

First, the researcher asks two open-ended questions about religion in general: (1) “When I say the word ‘religion,’ what do you think of? Can you explain what ‘religion’ means?”; and (2) “There are lots of different religions in the world. Can you tell me all the religions you’ve heard of?”

Then, the researcher asks an open-ended question about the child’s family’s religious identity. In some cases, this question is phrased as, “What about your family: Does your family belong to a certain religion?”; in other cases, the question is instead phrased as, “Does your family believe in a certain religion?” Researchers are allowed to ask both questions if they deem it appropriate, and these judgments are generally made in real time on a case-by-case basis. If the child indicates that their family does belong to or believe in a religion, the researcher follows up with the question, “Which religion?” If the child indicates that their family does not belong to or believe in a religion, the researcher follows up with the question, “Do you mean they don’t belong to a religion at all, or do you mean you don’t know which religion?” If at any point the child indicates that they are not sure how to answer the question, the researcher can choose to ask a pair of additional follow-up questions: “What does your family believe in? Does your family ever go to church, or synagogue, or temple, or mosque or anything like that?”

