Caregivers in the US are given a few additional sample-specific instructions intended to clarify how we expect them to complete the task: “In this activity, we really want to get a sense of how you and your child talk about things together. We know in other activities we’ve asked you not to influence your child’s responses to our questions. We are not worried about that here. In this activity, please just interact with your child the way you normally would. Next you’ll see the list of all the questions that will come up in this activity. Don’t start your conversations just yet. We just want you to know what kinds of questions may come up.” Caregivers then proceed to the standard instructions and stimuli described in the previous section.

When we first began data collection in the US, caregivers were emailed instructions about how to complete and record this task independently and asynchronously without researcher supervision. At this point in data collection, we instead administer this task to caregivers and children via live video chat at the end of the Child Protocol. Analyses of data from this task will take into account differences across participants in the mode of study administration; in the US, this will include noting which caregivers completed the task independently vs. via live video chat with a researcher.

*Related tasks for parents/caregivers*. In the Parent Survey, parents/caregivers are asked to reflect on the Caregiver-Child Conversation task. For each of the six conversation topics included in this task, the survey-taker (i.e., the child’s parent/caregiver) is asked how “natural” it would be for the child to discuss that topic with the caregiver who participated in the task; whether the participating caregiver chose to discuss or to skip that topic in the course of completing the task, and why/why not; whether the survey-taker had discussed that topic with that child before the child completed the task; and whether there was anything that surprised them about the child’s conversation about that topic.

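### In the US samples session format follows age, so planned age main effects on tasks in Part 2 of the Child Protocol are partly confounded with one-day versus two-day testing

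*Protocol article*

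**What the plan says.** The Fig 2 legend (Overview, Protocol components) describes two formats. The split format applies "in two testing sessions on different days for other children (including all US children under the age of 8 years"). Its counterpart, with both parts done on one occasion, is described thus: "administered in the same testing session for some children (including most US children 8 years old or older"). The US eligibility section sets the age range: "Participating children must be between the ages of 4 years 0 months and 10 years 11.99 months".

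The section on the Developing Belief Network describes Wave 1 as a stage "which will shed light on development via cross-sectional comparisons of ages"; longitudinal analysis is left to later waves. The planned-analyses sections accordingly list age main effects or age interactions for most tasks. For Direct questions about religion they plan a main effect of age on the likelihood of a correct self-identification. That section also says of its position: "This is the final task in the Child Protocol".

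No planned-analyses section for a Child Protocol task mentions session format. The Caregiver-Child Conversation task, which is a separate component, does deal with a related matter: "Analyses of data from this task will take into account differences across participants in the mode of study administration".

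**The concern.** Below age 8 format does not vary. Above 8 it is mostly the other format. A child under 8 starts Part 2 on a different day from Part 1. Most older children start it straight after Part 1. Fatigue, time elapsed since Part 1, and carry-over from earlier tasks can therefore all differ by age for reasons that have nothing to do with development.

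A linear age term fitted across 4–10 years takes up part of any such difference, and a step at age 8 could be read as a developmental change. Because Wave 1 has only between-child age comparisons, nothing else in this wave separates the two. The data are also to be shared, and later users would meet the same problem without warning unless session format travels with the dataset.

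**Working it through.** The plan gives no figure to reproduce here. The check has three steps.

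**1. Length of a single sitting (oldest US children, minutes, from the task sections).** Sorting 4–9; Property Attributions 8–13; Religious Indicators 4–8; Social Essentialism 3–6; Norm Violations 7–11; Direct questions 2–4; Justifications 6–14; Child as Transmission Agent 4–10; Memory Span 4–10.

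- Lower ends: 4+8+4+3+7+2+6+4+4 = 42.
- Upper ends: 9+13+8+6+11+4+14+10+10 = 85.
- Direct questions comes last, so a one-session child reaches it after 42−2 = 40 to 85−4 = 81 minutes of tasks. A two-session child has done part of that on another day.

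**2. How closely format follows age.** Assumptions: ages uniform on 4 to 11; a share s of children aged 8+ tested in one session. The document says only that most are, so s runs from 0.51 to 1.

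- Variance of age = 7²/12 = 4.083; SD = 2.02.
- Share aged 8+ = 3/7; mean ages above and below 8 are 9.5 and 6.0, a difference of 3.5.
- Cov(age, one session) = s × (3/7)(4/7) × 3.5 = 0.857s.
- Slope of P(one session) on age = 0.857s / 4.083 = 0.21s per year.
- r = 0.857s / (2.02 × √[(3s/7)(1−3s/7)]); variance inflation factor (VIF) = 1/(1−r²); the SE of a format-adjusted slope grows by √VIF.

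**3. Bias in an unadjusted age main effect.** A one-session effect of d SD adds 0.21s × d per year, or six times that between ages 4 and 10.

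| s | r | VIF | SE factor | bias per year | bias over 6 years |
|---|---|---|---|---|---|
| 1.00 | 0.86 | 3.8 | 1.9 | 0.21d | 1.26d |
| 0.90 | 0.79 | 2.6 | 1.6 | 0.19d | 1.13d |
| 0.75 | 0.68 | 1.9 | 1.4 | 0.16d | 0.94d |
| 0.51 | 0.52 | 1.4 | 1.2 | 0.11d | 0.64d |

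With an assumed d = 0.2, the shift between ages 4 and 10 is 0.64 × 0.2 = 0.13 SD to 1.26 × 0.2 = 0.25 SD.

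For a sense of what that does to a test, assume d = 0.3, no true age effect and residual SD 1. The expected z is 0.21s × 0.3 × 2.02 × √N. At N = 450, the planned US minimum, this is 2.70 for s = 1, and a nominal 5% test rejects with probability 0.77; for s = 0.51 it is 0.28. In one sample of 75 the figures are 0.20 and 0.09. These probabilities rest entirely on the assumed d. For Direct questions the outcome is correct or incorrect, so d must be read on a standardised scale.

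**The case against.** Several points on the other side stand.

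- **Reach.** A reader might infer that nearly every age test in the protocol is compromised. The text does not support that. Only tasks in Part 2 are exposed in this way, and the split between parts is in Fig 2. From the text alone, only Direct questions is certain.
- **Interactions.** The slope bias should not be carried over to tests such as the Social Essentialism "statistical interactions between domain (gender, religion, wealth) and participant age (4–10 years"). These are built on within-child contrasts. A format effect that shifts all conditions equally on the analysis scale cancels, and only one that differs by condition biases the interaction. That could arise where a contrast straddles the break between parts. The two Child as Transmission Agent blocks come at different points in the protocol, but whether the break lies between them is not known from the text.
- **Direction.** A reader might infer that a spurious age effect is the likely result. Fatigue and shorter answers in older children would more naturally mask the predicted increases with age. Carry-over could act the other way, since the target group's label is used in several tasks before the self-identification questions. The documents give neither sign nor size.
- **Design.** Splitting the sessions for young children may itself reduce an age-related fatigue difference that one long sitting for everyone would cause. The split is therefore not criticised here.
- **Exploratory article.** The plan calls itself largely exploratory and its listed tests the most basic ones, and it nowhere says that format will be ignored. This lowers the weight of the point. It does not remove it: the article sets out its age tests task by task and allows for administration mode in one component, but not in the component where format is tied to age.

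**Conclusion.** The point holds in limited form. In the US samples, planned age main effects on Part 2 tasks are partly confounded with session format: certainly for Direct questions about religion, and for other tasks as Fig 2 determines. The size is about 0.11d to 0.21d SD per year for a format effect of d SD, assuming uniform ages and 51–100% of children aged 8+ tested in one session. Whether this hides or creates an age effect cannot be told from the documents.

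The confounding is not total. Format is constant among under-8s, and children aged 8+ tested in two sessions give some overlap if there are any. Other countries' session formats are not described, so nothing is claimed about them.

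It would go too far to let an age effect be claimed only when the under-8 slope has the same sign. About 4/7 × 75 ≈ 43 children per minimum-size sample would be under 8. With an assumed true slope of 0.1 SD per year and residual SD 1, the SE is 1/(1.155 × √43) = 0.13, and the sign would be wrong about 22% of the time. Such a rule would also bar real change that occurs after 8.

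**What to change.** For age main effects on Part 2 tasks in the US samples, state that the planned estimate will be accompanied by two sensitivity analyses:

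1. the age slope among children under 8, where format is constant;
2. a model that adds a one-/two-session indicator, with a note that children aged 8+ tested in two sessions may be a selected group, and that if there are none the format term is identified only by assuming the shape of the age trend.

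Carry session format as a variable in the dataset; the article does not say that this is done. Where the estimates differ materially, caution readers against taking a change at age 8 as development. For age interactions, a comment is needed only where the format effect could plausibly differ by condition.

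Cost: some added analysis and reporting, no change to data collection sessions, and an adjusted slope whose SE is about 1.2 to 1.9 times larger. That loss of precision is why these analyses should stand beside the planned estimate and not replace it.
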